### 9.2 Definition of evaluation collectives

The primary analysis will be performed according to the intention-to-treat (ITT) principle - i.e. in all included patients. Sensitivity analyses will be performed in the per-protocol (PP) collective, for which rules will be defined prior to study completion.

### 9.3 Planning the scope of the study (case number planning)

Case number planning was performed for the primary end point, 30-day mortality, using the simulation software of Reich et al (25). A systematic review and meta-analysis were performed for case number planning (26). The meta-analysis, although not including any randomized trials, allowed estimation of the probability of patient death (within the 30 days starting from the time of SAB diagnosis) in the intervention vs. control group. This probability was estimated to be between 0.25 and 0.5 for the intervention group and between 0.5 and 0.7 for the control group. These probabilities translate into a relative risk of ~0.5. To detect such an effect with a power of >80% at a two-sided significance level of  $\alpha=5\%$  and low to moderate variation between study centers in the given design, at least 15 centers need to include an average of 2x15 patients (30 patients per cluster results in a total case number of 15x30=450 patients to be included). Since the follow-up visits consist only of telephone visits, which can also be answered by relatives of the patients, a low drop-out rate can be expected during the course. In order to be prepared for a possible drop-out, a total number of 500 patients is targeted.

## 9.4 Interim evaluation

Interim evaluations of the data are not provided.

## 9.5 Statistical analysis

Differences in the primary end point, 30-day all-cause mortality, are determined confirmatorily within the framework of a generalized linear mixed model (GLMM). This was specified in more detail by Reich et al (25) and also forms the basis of the case number calculation. This model is suitable to represent the dependence structure by the clusters and the period effects for a dichotomous outcome variable, where the null hypothesis of no treatment effect can be rejected if the two-sided p-value of the Wald test statistic for the fixed effect *group* can be rejected at the two-sided significance level  $\alpha=5\%$ . The confirmatory test is performed according to the ITT principle, with missing endpoint data in included patients replaced by multiple imputation. Further sensitivity analyses of the primary endpoint are "worst case" imputations as well as analyses in the PP collective. In addition, the *a priori* defined subgroups center, gender and age groups (quartiles) of the patients will be analyzed stratified. For these analyses as well as for the adequate statistical analyses of the secondary endpoints, which will also be performed within GLMM, no multiplicity adjustment is planned.

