| Target population/disease             | Patients with Staphylococcus aureus bacteremia.                                                                                                                                                                                                                                                                                                                                                                                                                                                                                                                                                                                                                                                |
| Study design/methodology              | Prospective randomized, single-blind, controlled two-arm (intervention vs. control) multicenter trial with cross-over design. The intervention is the provision of a non-requested infectious disease telephone consult. The control group will not receive a telephone consult. The study duration in one group before cross-over is to be 12 months.
Randomization: 1:1 cross-over
Blinding: simple, i.e., patients are not told which group (intervention or control) they are in; blinding of treating physicians/study centers is not possible.
Intervention group: non-requested telephone consult.
Control group: no telephone consultation, follow-up only.
Follow-up: 90 days |
| Aims of the clinical trial/objectives | Primary Objective:
To demonstrate efficacy (30-day all-cause mortality) and safety of nonrequested infectious disease consults compared with standard care without telephone consults in patients with SAB.                                                                                                                                                                                                                                                                                                                                                                                                                                                                                 |

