## 6 Patient selection

### 6.1 Inclusion criteria

All adult (at least 18 years old) patients, regardless of gender, with diagnosed SAB (positive blood culture) who have given their written consent to participate in the study should be included. Re-enrollment of a patient who had already been included in the study will only occur if the 2nd SAB episode occurs more than 90 days after the 1st SAB episode and there is no evidence of recurrence due to deep-seated infection. In this case, the patient will be re-educated and must again consent to study participation. In principle, he will be managed as a new patient. It must be noted in the patient file and in the CRF that this is a 2nd SAB episode.

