## 7 Course of studies

### 7.1 Detailed study process

Information about a microbiological blood culture result *positive* for *S. aureus* is automatically reported to the SUPPORT team via the AlertsNet infrastructure (Electronic Blood Culture Registry, EBCR). However, data management is done separately. The system sends a fax to the treating hospital with the patient's clinical name, -year of birth, *subject identification code* (SIC) and microbiological findings. The study center at the UKJ, which is informed at the same time, does not receive any clear name information but only the information of a SAB detection in a specific institution and the automatically generated case code (SIC). The study center contacts the study physician at the clinical institution and, based on the relevant positive microbiological findings and using the SIC, asks for the patient to be included in the study. If the patient agrees to participate in the study after being informed by the study physician, the signed consent form is faxed to the study center. Only with this fax does the study center thus receive clear name information on the SAB-positive patient. Thereupon, for patients of the intervention arm, the telephone consultation with the treating physician is performed and subsequently the consultation is confirmed by fax (incl. therapy proposal). For patients in the control group (no infectious disease consultation), the two aforementioned steps are omitted. After inclusion in the study, only the informed consent form is faxed to the study center. A consultation is not performed for these patients.

The SUPPORT study nurse documents the data of the study patients pseudonymously in the CRF as soon as possible during her on-site visits. After 30 and after 90 days, a follow-up call is made to the patients by the study center. The contact details for this are recorded separately in the consent form (**Figure** and **Section 14.2**).

[figure not shown]

\*EBCR: Electronic Blood Culture Registry

325

326 **Figure:** Flow chart for the SUPPORT study.

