## 327 Checking the inclusion and exclusion criteria

328 The examination of the inclusion and exclusion criteria of potential study patients  
329 ("screening") is performed using a predefined checklist. All patients who meet the inclusion  
330 criteria are documented in a central "Screening Log" (**Appendix 2**) at the study center. This  
331 log will also indicate whether the patient was included in the study or for what reason, if any,  
332 the patient was not included. If a patient fulfills all inclusion criteria and there are no exclusion  
333 criteria, he/she is to be entered in the patient identification list with the date of study  
334 inclusion.

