#### 10.3.2.5 Infection focus

- Intrathoracic infection
- Urogenital/renal infections
- Infection of the central nervous system
- Bone and joint infections
- Infections of the cardiovascular system

- 566 -HNO/oropharyngeal infections
- 567 -Intraabdominal infections
- 568 -Skin and soft tissue infections
- 569 -Postoperative wound infections
- 570 -Flexure tube as suspected source of infection
  
- 571 10.3.2.6 Characteristics of blood culture
- 572 -Date of blood culture collection
- 573 -Location of blood culture collection
- 574 -Presence of foreign bodies or prostheses
- 575 -Further positive blood cultures
- 576 -Detection of other bacteria
  
- 577 10.3.2.7 Presence of SIRS criteria
  
- 578 10.3.2.8 Organ dysfunction within 7 days of 1st positive blood culture.
- 579 -Acute encephalopathy
- 580 -Thrombocytopenia
- 581 -Arterial hypoxemia
- 582 -Renal dysfunction
- 583 -Metabolic acidosis
  
- 584 10.3.2.9 Septic shock within 7 days after 1. positive blood culture.
  
- 585 10.3.2.10 Severity of SAB
- 586 -uncomplicated
- 587 -complicated
  
- 588 10.3.2.11 PITT score on the day of blood culture collection (24).
  
- 589 10.3.2.12 Charlson comorbidity index (23)
  
- 590 10.3.2.13 Recommended measures/implementation of the recommended measures
- 591 -Time
- 592 -Follow-up blood cultures
- 593 -Focus remediation
- 594 -Transesophageal echocardiography
- 595 -other proposed measures
  
- 596 10.3.2.14 Laboratory values on the day of the positive blood culture
- 597 - Creatinine
- 598 -Creatinine Clearance
- 599 -Bilirubin
- 600 -Lactate
- 601 -CRP
- 602 -PCT
- 603 -ALAT
- 604 -ASAT
- 605 -AP
- 606 -leukocytes
- 607 -platelets
- 608 -neutrophil granulocytes
- 609 -Ferritin

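### Unblinded hospitals select and consent patients in a known phase, but the confirmatory model in 9.5 is described with group, cluster and period only and no planned analysis addresses phase-dependent selection

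*Protocol*

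**What the plan says.** **Allocation and blinding.** Hospitals are randomised to A-B or B-A before the study starts (Protocol 4.2, 7.3). Patients are blinded, but "blinding of treating physicians/study centers is not possible" (1.4 Synopsis).

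**Inclusion.** After a positive culture, the study centre asks the local study physician to include the patient. "If the patient agrees to participate in the study after being informed by the study physician, the signed consent form is faxed" to the study centre, and in the intervention phase the consult follows (7.1). In the control phase, inclusion leads to data recording and follow-up only. Section 6.1 covers adults with SAB "who have given their written consent to participate in the study should be included". The exclusions in 6.2 include palliative care, treatment limitation and a life expectancy under 90 days.

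**Analysis set.** ITT means all included patients (9.2), while the 30-day clock starts at SAB diagnosis (9.1).

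**Model.** On the confirmatory model, 9.5 says "This model is suitable to represent the dependence structure by the clusters and the period effects for a dichotomous outcome variable", with the decision resting on a Wald test of the group effect. It refers to a cited methods paper for further detail. The sensitivity analyses named for the primary endpoint are worst-case imputation and the per-protocol set. Age and gender appear only as stratified subgroups.

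**Baseline data.** Charlson index, Pitt score and demographics are listed in 9.1 as other recorded parameters. Under 10.3.2.11 the Pitt score refers to the day of culture collection, so it precedes the consult.

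**Screening log.** A central log lists patients who meet the inclusion criteria. According to the part of 7.1 on checking the criteria, this "log will also indicate whether the patient was included in the study or for what reason, if any", not.

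**The concern.** In a cluster trial, randomisation protects the comparison of hospitals. It protects the comparison of patients only if recruitment does not depend on the arm. Here the person who judges life expectancy and treatment limits, and who decides how hard to pursue consent (from a proxy or guardian if the patient lacks capacity), knows whether inclusion will bring specialist advice or follow-up only.

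The crossover cancels a hospital's stable habits of inclusion. It does not cancel a change of habit between that hospital's two phases. Deaths between diagnosis and consent also leave the analysis, possibly at different rates by phase.

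Any resulting difference in case mix enters the mortality contrast directly, and nothing planned in 9.5 would reduce or expose it, although strong predictors of death are already on the CRF.

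**Working it through.** **1. The plan's own figure.** Section 9.3: "To detect such an effect with a power of >80% at a two-sided significance level of" 5%, for 15 centres × 2 × 15 = 450 patients, i.e. 225 per condition. As a first check, ignoring clustering:

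power = Φ{(|p₁−p₂| − 1.96·s₀)/s₁}, where s₀ = √(2p̄(1−p̄)/225) and s₁ = √((p₁(1−p₁)+p₂(1−p₂))/225).

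For 25% vs 12.5%: s₀ = 0.0368, s₁ = 0.0363, argument 1.46, power 0.93. The same formula gives 0.96 for 27% vs 13% (rates in 2.3), 0.99 for 70% vs 50%, above 0.99 for 50% vs 25% (both pairs within the ranges in 9.3), and 0.76 for 25% vs 15%. A simulation of the crossover design (1,000 runs per setting; random hospital intercept, fixed group and period, Wald test) agrees. The stated bound of over 80% is therefore reproduced at a relative risk near 0.5 and at these planned rates.

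**2. Type I error under selection.** None of these inputs is in the documents; all are assumptions: 25% mortality in both conditions, hospital SD 0.3 on the logit scale, a prognostic score with log-odds 1.0 per SD, and intervention-phase patients healthier by the stated shift. The complete-score and half-score settings were run separately, so the unadjusted rate appears twice.

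| Shift (SD) | Unadjusted (two sets) | Adjusted, complete score | Adjusted, score with half of prognosis |
|---|---|---|---|
| 0.1 | 8.1%, 5.5% | 5.9% | 5.2% |
| 0.2 | 11.4%, 14.4% | 5.1% | 7.9% |
| 0.3 | 20.1%, 20.5% | 4.1% | 8.7% |

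Monte Carlo error is about 0.7 point near 5% and 1.3 points near 20%. With a weaker score (log-odds 0.7), the unadjusted rates run from 5.0% to 13.9%, and the adjusted rates do not exceed 7.1%.

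Check by hand for 0.3 SD: simulated mortality was 20.6% vs 25.1%, a gap of 4.5 points. SE = √(0.2285 × 0.7715 × 2/225) = 0.0396, so z = 1.14, and Φ(1.14−1.96) + Φ(−1.14−1.96) ≈ 0.21, in line with the table.

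**3. The same risk as inclusion fractions.** Assume that 25% of eligible patients are high risk (50% mortality, against 15% for the rest), that 90% of the others are included in both phases, and that high-risk patients are included at 90% in the intervention phase and 70% in the control phase.
- Control phase: high-risk share 0.175/(0.175+0.675) = 20.6%; mortality 0.15 + 0.35 × 0.206 = 22.2%.
- Intervention phase: share 25%; mortality 0.15 + 0.35 × 0.25 = 23.75%.
- Gap 1.5 points with no treatment effect; z = 0.0154/0.0397 = 0.39; type I error about 7%.
- At 60% control-phase inclusion: share 18.2%, mortality 21.4%, gap 2.4 points, type I error about 9%.

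Here the bias runs against the intervention; in step 2 it runs in favour. Both directions are plausible.

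**4. Power, unadjusted → adjusted** (complete score; log-odds 0.7 / 1.0 / 1.4 per SD; no selection).
- 70% vs 50%: 99.2→99.7 / 99.1→99.7 / 99.3→100%.
- 27% vs 13%: 96.3→97.4 / 95.4→97.3 / 96.6→99.0%.
- 25% vs 12.5%: 94.0→95.0 / 93.7→97.2 / 92.7→96.7%.
- 25% vs 15%: 77.4→80.3 / 77.8→80.1 / 77.2→86.7%.

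**5. Can the data carry the model?** Expected deaths at 25% vs 12.5%: 225 × 0.25 + 225 × 0.125 ≈ 84, enough for three covariates.

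**The case against.** **Silence is not exclusion.** Section 9.5 does not rule covariates out, defers detail to a cited paper, and an analysis plan may add them. An unadjusted primary test on the model used for sizing is also a legitimate choice. This stands in part. But 9.5 goes beyond a general outline: it describes the confirmatory model and names its sensitivity analyses, and neither of these bears on recruitment in a known phase. Covariates also change the odds ratio being tested, so they belong with the confirmatory test.

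**The design has safeguards.** Alerts are automatic, the study centre itself asks for inclusion in either phase (7.1), proxy or guardian consent is allowed (7.2), and crossover removes stable differences between hospitals. All true. They limit selection and make it partly visible, but they do not act on phase-dependent decisions within a hospital.

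**The log already covers non-inclusion.** A reader might infer that refusals and deaths before consent go unlogged, because the log takes patients who meet the inclusion criteria and 6.1 makes consent one of them. The documents do not settle this: the synopsis criteria omit consent, 10.3.2.1 lists consent separately from the criteria, and the log must give reasons for non-inclusion. The wording is ambiguous, not clearly deficient.

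**The trial does not need the power.** A reader might infer that omitting covariates leaves the trial underpowered. At a relative risk near 0.5, unadjusted power exceeds 90%; only a smaller effect such as 25% vs 15% falls short of 80%. This objection stands.

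**Covariates cannot fully correct selection.** This also stands: they act only on measured prognosis and cannot bring back patients who died before consent.

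**Conclusion.** The point holds as a design risk that the described analysis leaves unaddressed. Recruitment in a known phase, judgement-based exclusions and the absence of any patient-level term or selection-related sensitivity analysis in 9.5 are all in the text. The size rests on assumptions: for shifts of 0.1 to 0.3 SD at log-odds 1.0, type I error is about 6% to 20% unadjusted, about 5% adjusted for a complete score, and at most about 9% adjusted for a half-complete one.

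Two stronger readings are not supported. One is that the comparison is biased, or biased towards the intervention: the documents show neither selection nor its direction. The other is that adjustment would put the problem right: it would reduce it. Any power gain is secondary, about 0.5 to 4 points at a relative risk near 0.5 or at the planned rates, and about 2 to 10 points at 25% vs 15%.

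The change should be made because it is cheap and must be prespecified to be credible.

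**What to change.** - **Section 9.5:** include Pitt score, Charlson index and age as fixed effects in the confirmatory GLMM beside group and period. Keep the unadjusted model as a sensitivity analysis, and report a standardised risk difference beside the odds ratio.
- **Section 7.1, checking of criteria:** state that the log covers every *S. aureus* alert, with the hospital's phase, and with refusal and death before consent as listed reasons. A code is generated for each finding (10.4), so this is feasible.
- **Reporting:** give inclusion fractions and baseline characteristics by phase.

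**Cost:** wording and log entries, with no new clinical measurements. The adjusted odds ratio is conditional on the covariates, so it differs from the unadjusted one even without selection; the standardised risk difference helps the reader here. A few missing covariate values will need imputing, which fits the multiple imputation already planned for the endpoint. The log and the inclusion fractions, not the model, are what would show losses before consent.

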## 48 1.2 Introduction of a wash out phase

49 In addition to the specifications made in the study protocol (version 1.07 of 18.05.2016)  
 50 regarding randomization and inclusion of patients in the intervention and control groups, a  
 51 one-month wash-out phase will be introduced between the end of the intervention phase  
 52 (after the inclusion of 15 patients in one institution) and the start of the control phase (before  
 53 the inclusion of 15 additional patients in the institution who are educated but do not receive a  
 54 consil). This phase is intended to ensure that knowledge of improved treatment strategies  
 55 gained during the intervention phase approaches pre-study routines, allowing clearer  
 56 differentiation between outcomes the intervention and control phases. Accordingly, no wash  
 57 out phase is required between the end of the control phase and a subsequent intervention  
 58 phase.

59

60

61

---

62 [name].med. **[name]**, Head of the study Date

63

64

65

---

66 **[name]**, M.D., Deputy Study Director Date

67

68

69

70 *[name].med. **[name]**, Biometrician*

Date

71

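### The confirmatory model names hospital clusters and period effects but no hospital-by-period variation, so its 5% level depends on hospitals not shifting differently between phases; separately, no listed analysis checks whether the one-month wash-out removed carry-over

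*Protocol*

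**What the plan says.** **Model and test.** Section 9.5 analyses 30-day mortality in a GLMM and says that "This model is suitable to represent the dependence structure by the clusters and the period effects for a dichotomous outcome variable". The null hypothesis is rejected on the "two-sided p-value of the Wald test statistic for the fixed effect *group* can be rejected at the two-sided significance level" of 5%. For detail the section points to a cited methods paper: "This was specified in more detail by Reich et al (25) and also forms the basis of the case number calculation".

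**Planning.** Section 9.3 gives the variance assumption only as "low to moderate variation between study centers in the given design", with no number, and concludes that "at least 15 centers need to include an average of 2x15 patients". No variation between phases within a hospital is mentioned.

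**Timing of the switch.** Sections 4.2 and 5 let each hospital cross over individually, after its 17th patient or after one year at the latest. (Section 4.3 instead describes a switch after 250 patients overall or 12 months, and the wash-out amendment refers to 15 patients per phase.)

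**Carry-over.** Section 1.2 of the amendment says that a "one-month wash-out phase will be introduced between the end of the intervention phase" and the control phase, so that knowledge gained from the consults can recede. No wash-out applies in the other direction.

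**Sensitivity analyses.** Section 9.5 lists worst-case imputation and the per-protocol set, plus subgroups by center, gender and age quartile.

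**The concern.** In a cluster crossover, patients of one hospital in the same phase tend to be more alike than patients of that hospital in different phases, because staffing, case mix and local outbreaks change over months. Individual switching strengthens this: phase 1 covers different calendar windows and lengths in different hospitals. A common period effect removes only the shift that all hospitals share. Hospital-specific shifts stay in the treatment contrast. If the model has no term for them, the standard error is too small, the interval too narrow and the 5% level of the only confirmatory test is not held.

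Carry-over is a different harm. If A-B hospitals keep using what they learned, their control phase looks partly like intervention and the estimated effect shrinks. The amendment takes this seriously enough to change the design, yet nothing listed would show whether one month sufficed.

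**Working it through.** **Inputs from the protocol.** 15 hospitals x 2 phases x 15 patients = 450; 1:1 to A-B or B-A; two-sided 5% Wald test (9.3, 9.5, 4.2). Mortality of 0.25-0.5 vs 0.5-0.7 (9.3); 13% vs 27% (2.3); 22-26% at 30 days (1.3).

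**Assumptions, because the protocol gives no figure.** Hospital random-intercept SD 0.3; hospital-by-period SD τ from 0 to 0.5 (logit scale).

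**1. The plan's own figure.** Section 9.3 states "To detect such an effect with a power of >80% at a two-sided significance level of" 5%. Simple two-proportion power with n = 225 per arm is Φ[(|p₁−p₂| − 1.96·√(2p̄(1−p̄)/n)) / √((p₁(1−p₁)+p₂(1−p₂))/n)]. For 27% vs 13% this is Φ[(0.14 − 1.96×0.03771)/0.03713] = Φ(1.78) = 96.2%. The simulated GLMM Wald test at τ = 0 gives a similar result:

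| Control vs intervention | Formula | Simulated GLMM |
|---|---|---|
| 0.50 vs 0.25 | >99.9% | 100% |
| 0.70 vs 0.50 | 99.2% | 99.3% |
| 0.27 vs 0.13 | 96.2% | 96.1% |
| 0.25 vs 0.125 | 92.7% | 92.6% |

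So power above 80% is confirmed. That 450 is the minimum cannot be reproduced, because the between-center variance is not stated.

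**2. What hospital-by-period variation adds.** The group effect is half the difference between sequences in mean within-hospital change. Each change carries extra variance 2τ². With 7 and 8 hospitals per sequence, the added variance is ¼·2τ²·(1/7 + 1/8) = 0.134τ².

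At 25% mortality and τ = 0.5, the model's mean SE is 0.220 (variance 0.0486) and the added variance is 0.0335. The true SD is then about √0.0821 = 0.287; the simulation gave 0.283. The test in effect rejects at |z| > 1.96×0.2204/0.2865 = 1.51, a two-sided error of about 13%.

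**3. Simulated type I error** (3,000 runs per setting, Monte Carlo SE about 0.4 points at 5%). The model has a hospital intercept, common period effect, group effect and Wald z-test:

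| τ | 25% mortality | 50% mortality |
|---|---|---|
| 0 | 4.6% | 5.8% |
| 0.2 | 5.5% | 6.2% |
| 0.3 | 7.6% | 8.8% |
| 0.5 | 12.1% | 14.6% |

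A separately coded run at 25% mortality gave 5.0 / 6.4 / 7.6 / 11.6% for the same four values of τ.

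**4. With the variation allowed for.** A period-adjusted t-test on within-hospital differences, with 15 − 2 = 13 df, held 4.5-5.5% for every τ up to 0.7 at both mortality levels. A GLMM with a hospital-by-period random effect and 13 df gave 4.8-5.0% (assumed ICC 0.05-0.10, between-phase correlation 0.5-0.8).

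**5. Carry-over.** Suppose a fraction c of the log odds ratio persists in the control phase of A-B hospitals. The within-hospital contrast then estimates (1 − c/2) of the true effect. For 27% vs 13%, with τ = 0 and 1,000 runs:

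| c | Mean log OR | OR | Power |
|---|---|---|---|
| 0 | −0.92 | 0.40 | 96% |
| 0.5 | −0.70 | 0.50 | 79% |
| 1 | −0.50 | 0.61 | 48% |

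Check at c = 0.5: 0.75 × (−0.915) = −0.69. Under the null there is no effect to carry over, so type I error is untouched.

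**The case against.** **The model may contain more than the protocol names.** A reader might infer that the model carries only hospital clustering and a period effect common to all hospitals. Section 9.5 does not say that: it refers to a cited paper for the detail, and an analysis plan may add terms. This stands. The point is about what the protocol names. It is still fair to raise, because 9.5 itself fixes the model, test and level and declares the dependence structure covered.

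**About 15 hospitals is too few for a plain Wald test.** A reader might infer this too. The figures do not support it: at τ = 0 the error is 4.6-5.8%. Section 9.5 also fixes no reference distribution, and 15 is a minimum out of up to 39 hospitals. The small-sample reference belongs to the remedy; its absence is not the fault.

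**The inflation rests on assumed variances.** True. At τ = 0.2 the excess is about 0.5 to 1.5 points, and a shift shared by all hospitals does no harm.

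**Carry-over is partly handled, and a null result would still be readable.** The wash-out covers the one direction in which consult learning can persist, and control phases of B-A hospitals precede any consult there. The bias is towards null. At the planning rates in 9.3, a simulation with 50% carry-over still gave 98% power (0.50 vs 0.25) and 93% (0.70 vs 0.50), though those rates lie well above the 22-26% mortality in 1.3. So it would be too strong to say that a negative result could not be interpreted; it would be harder to read.

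**Conclusion.** The concern holds in conditional form. With the terms that section 9.5 names, read as a hospital intercept and a common period effect, type I error is about 5.5-6.5%, 7.5-9% and 12-15% at hospital-by-period SDs of 0.2, 0.3 and 0.5, and intervals are too narrow. Those SDs are assumptions, as is the hospital SD of 0.3. Individual switching over up to 12 months makes some such variation plausible, but the protocol gives nothing from which to estimate it.

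The lack of a carry-over check is a separate and milder gap. It threatens power and the reading of a null result, not the 5% level. Its size depends on an assumed carry-over fraction and on using 27% vs 13%.

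This is a worthwhile, inexpensive improvement to the plan, not a demonstration that the trial's test is invalid.

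**What to change.** **In section 9.5, state the confirmatory model:** a logistic GLMM with fixed group and period, random hospital and random hospital-by-period effects, and the group effect referred to t with hospitals minus 2 df. An equivalent cluster-period analysis would also serve.

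**Pre-specify two carry-over sensitivity analyses:** (a) the group comparison in phase 1 only; (b) quality-indicator fulfilment in control phases of A-B versus B-A hospitals. State that a null primary result will be interpreted in the light of both.

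**Cost.** No new data are needed, since quality indicators are already a secondary endpoint. Some power is lost. For 27% vs 13%, the 13-df cluster-level test has about 93%, 88% and 77% power at hospital-by-period SDs of 0, 0.3 and 0.5, so at the largest it falls below the 80% target. The uncorrected test shows 96%, 95% and 91%, but at the two larger SDs it does so with an inflated error rate. The phase-1 comparison discards half the data and relies on between-hospital contrasts, so it will be imprecise and can only support interpretation.
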